**Abstract of Research Scheme**

| Research topic | The Efficacy and Safety of Miconazole Nitrate 10mg Mucoadhesive Tablets Verus Itraconazole Capsules in the Treatment of Oral Candidiasis: A randomized, open label, multicenter phase III trial |
| --- | --- |
| Research objectives | To evaluate the Efficacy and Safety of Miconazole Nitrate 10mg Mucoadhesive Tablets in comparison with Itraconazole Capsules |
| Research design | A randomized, open label, multicenter phase III trial |
| Inclusion criteria | The inclusion criteria: 1) age range of 18-70 years; 2) diagnosis of oral candidiasis was established based on clinical manifestation and laboratory testing (smear test and/or fungi culture); 3) negative reaction to pregnancy test in women and willing to take effective method of birth control in the period of trial. |
| Exclusion criteria | The exclusion criteria: 1) systemic fungal infections or chronic mucocutaneous candidiasis; 2) a history of a known allergy or intolerance to miconazole nitrate and/or itraconazole; 3) use of rifampicin, rifabutin, isoniazid, phenobarbital, phenytoin, methylprednisolone, carbamazepine, terfenadine, astemizole or cisapride; 4) history of psychological or other disorder that unable to cooperate; 5) Abnormal liver and kidney function; 6) history of cardiac disorders such as ischemic heart failure; 7) history of hematological diseases; 8) use of systemic or topical antifungal therapy within 2 weeks before study entry; 9) hyposalivation related disease or drug-taking; 13) HIV infection; 14) history of participating other clinical trials within 4 weeks before study entry. |
| Index of efficacy | Primary: Evaluation of clinical symptoms (pain and burning sensation rating), signs (pseudomembrane and erythema grade).  Scondary: Mycological eradication of organism (by smear test and fungi culture) |
| Index of Safety | Bood pressure, electrocardiography, full blood count and liver and kidney function |
| Dosage regimen | Miconazole Nitrate 10mg Mucoadhesive Tablets Itraconazole 100mg Capsules |
| Course of treatment | 2 weeks treatment and 2 weeks follow-up |

**1. Background**

Oral candidiasis is a common form of oral fungal disease. Terrible oral hygiene, xerostomia, HIV infection, and radiation therapy for head and neck cancer have resulted in a significant proportion of the population suffering from oral candidiasis. The accepted treatment for oral candidiasis is the use of polyenes, such as and not limited to amphotericin B and nystatin, and azoles including fluconazole, miconazole, itraconazole, and clotrimazole. The CDC, IDSA, NIH, and HIVMA emphasize that topical antifungal therapy should serve as first-line therapy for mild OPC. Currently available topical agents involving nystatin, amphotericin B and clotrimazole have limitations, such as short retention time on the oral mucosa and the need for multiple applications each day. Moreover, many topical agents contain sugar, which may affect the oral cavity and patients with systemic disorders. Fungal resistance is also a significant concern and common problem .

Miconazole is a synthetic imidazole antifungal regimen that has been used for nearly 40 years to effectively and safely treat superficial fungal infections. Miconazole can damage the integrity of the fungal cell membrane, alter fungal adherence, and inhibit the formation of germ tubes and mycelia. Miconazole has potent broad-spectrum activity against many *Candida* species, including *Candida albicans* (*C. albicans*)*, Candida dubliniensis* (*C. dubliniensis*)*, Candida parapsilosis* (*C. parapsilosis*)*, Candida glabrata* (*C. glabrata*)*, Candida famata* (*C. famata*) and *Candida tropicalis* (*C. tropicalis*). Furthermore, miconazole is also effective against species of *Candida* that are resistant to fluconazole (*C. albicans*, some *C. glabrata*). The recent availability of miconazole offers an alternative based on its various topical formulations, broad-spectrum activity, and less resistance. Various up-to-date topical formulations of miconazole have been used to treat oral candidiasis, including miconazole buccal tablets, miconazole chewing gum, miconazole oral gel, and miconazole lacquer.

However, although there were studies evaluating the effect of mucoadhesive tablet in treating special subgroups of patients with HIV infection or with head and neck cancer, the knowledge of its effectiveness and safety in the management of general oral candidiais patients, which is a rather larger group, is still insufficient. Therefore the aim of this study is to evaluate the effectiveness and safety of miconazole mucoadhesive tablet in treating oral candidiasis and to establish a standard therapeutic program for its application.

**2. Objectives**

To evaluate the the efficacy and safety of miconazole nitrate 10mg mucoadhesive tablets in comparison with itraconazole 100mg Capsules in the treatment of oral candidiasis.

**3. Research Methods**

3.1 Research design

This study is a randomized, parallel-armed, positive-controlled, open label clinical trial comparing mucoadhesive miconazole tablet and itroconazole capsules in adult patients with oral candidiasis. The study complies with the State Food and Drug Administration (SFDA) principles of China and Good Clinical Practice guidelines (GCP). Its reporting will be guided by the CONSORT statement.

3.2 Sample size

In the present data of studies on the efficacy of itroconazole treating oral candidiasis, an 85% efficacy rate was assumed. To achieve 80% power with a significance level of 10%(α level, 5%; βlevel, 20%; both 1-sided), 158 participants per group would be required. To compensate for a potential 20% dropout rate, a sample size of 380 participants in total will be applied for this study.

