11.2 Statistical analysis method

Analysis and reporting of the results will follow the CONSORT guidelines for reporting randomised controlled trials. All participants who had at least 1 efficacy evaluation after randomization will be included in the analysis. Safety analyses included all patients who received at least 1 dose of study medication. The trial data will be processed and analyzed by an independent statistician, who will be blinded to participant allocation.

A non-inferiority statistical approach was used. Continuous data were compared using either the Student t test or the Mann-Whitney nonparametric test. For binary data, the 2 treatment groups were compared using the chi-square test or the Fisher exact test. The Mantel-Haenszel test was used to evaluate ordinal quantitative data.

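### 380 patients cover at most 16.8% dropout, not the stated 20%, and section 3.2 gives the significance level as both 10% and 5%

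*Protocol*

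**What the plan says.** All the figures are in Protocol section 3.2. For the control drug, "an 85% efficacy rate was assumed". The error rates are given as "To achieve 80% power with a significance level of 10%(α level, 5%; βlevel, 20%; both 1-sided", and the result is that "158 participants per group would be required". The allowance for losses follows: "To compensate for a potential 20% dropout rate, a sample size of 380 participants in total will be applied for this study".

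Section 11.2 gives the type of comparison: "A non-inferiority statistical approach was used". The protocol states no non-inferiority margin, and no section other than 3.2 gives an alpha or a confidence level.

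Three other sections bear on what a dropout does to the analysis:

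- Section 11.1 defines the full analysis set (FAS) as randomised patients with at least one evaluation after medication, and fills later gaps by LOCF. It runs the efficacy analysis on both the FAS and the per-protocol set (PPS), which is limited to patients who complete treatment.
- Section 6.2 allows a withdrawn patient's last result to stand as the final one.
- Section 6.4 allows enrolment to end once the target size is reached.

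**The concern.** Two things in section 3.2 do not fit together.

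First, an allowance for 20% loss should leave the required number after 20% of those randomised are gone. Here it does not: 20% off 380 leaves fewer than 2 x 158. Because section 6.4 treats the target as a point at which enrolment may end, nothing elsewhere in the protocol makes up the difference.

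Second, one phrase attaches two values to the type I error: "significance level of 10%(α level, 5%; βlevel, 20%; both 1-sided". Both cannot be the one-sided error rate of the same test. The margin would normally show which value was used, but it is not given, so the reader cannot confirm the basis of 158 from the text.

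At stake are the accuracy of the power statement and a clear statement of the error rate behind a non-inferiority conclusion.

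**Working it through.** **Inputs from section 3.2:** 158 evaluable per group (316 in total); 20% dropout; 380 in total, taken as 190 per group; 85% efficacy; 80% power; alpha printed as 10% and as 5% one-sided. **Assumptions, not in the protocol:** 85% in both arms, and a 10-point margin (varied below).

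**1. Reproducing 380.**
- 158 x 1.2 = 189.6, rounded up to 190; 2 x 190 = 380. This matches exactly.

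**2. The total that covers 20% loss.**
- n / (1 - d) = 158 / 0.8 = 197.5, so 198 per group and 396 in total.
- Inflating the total instead: 316 / 0.8 = 395.
- 380 is therefore 15 to 16 patients short, about 4%.

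**3. What 380 delivers.**
- At 20% loss: 380 x 0.8 = 304, or 152 per group; 316 - 304 = 12 short.
- Largest loss that still leaves 316: (380 - 316) / 380 = 64 / 380 = 16.8%.

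Steps 1 to 3 need no assumption about alpha or margin.

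**4. Which analysis set is affected.**
- 20% of 380 is 76 dropouts. The FAS loses only those without a post-dose evaluation, and evaluation starts at the one-week visit (section 8.3).
- The FAS falls below 316 only if more than 64 of the 76 (64 / 76 = 84%) leave before any such evaluation.
- The PPS loses every patient who does not complete treatment, so the shortfall falls there first.

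**5. Reproducing 158.** For non-inferiority of two proportions with equal true rates, n per group = 2 x p(1 - p) x (z_alpha + z_beta)^2 / margin^2, with p(1 - p) = 0.85 x 0.15 = 0.1275.
- One-sided 5%, 10 points: 0.255 x (1.645 + 0.842)^2 / 0.01, which rounds up to 158. This matches exactly.
- One-sided 10%, 10 points: 0.255 x (1.282 + 0.842)^2 / 0.01, which rounds up to 115.

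Solving for the margin that gives 158:

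| One-sided alpha | Margin that gives 158 | n per group at 10 points |
|---|---|---|
| 5% | about 10.0 points | 158 |
| 10% | about 8.5 points | 115 |
| 2.5% | about 11.3 points | 201 |

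So 158 fits more than one pair of alpha and margin. One-sided 5% with a round 10-point margin is the natural pair, but it is inferred.

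**6. Power, one-sided 5%, assumed 10-point margin.** Power = Phi(0.10 / sqrt(0.255 / n) - 1.645).
- n = 158: Phi(2.489 - 1.645) = 80.1%.
- n = 152: Phi(2.441 - 1.645) = 78.7%.
- The loss is about 1.4 points.

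**The case against.** The strongest reply on dropout is that the protocol does not discard dropouts. Sections 6.2, 11.1 and 11.2 keep anyone with one post-treatment evaluation in the FAS, so 20% dropout need not mean 20% fewer patients analysed. This stands for the FAS: step 4 shows it would need very early loss on a large scale to fall below 316. A reader might infer that the trial misses its power at 20% dropout in every analysis, and the documents do not support that. The reply does not rescue the PPS, on which efficacy is also analysed and which matters in a non-inferiority comparison. Nor does it make 380 the right figure for the allowance that section 3.2 claims.

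On alpha, the bracket names 5% as the alpha level and calls it one-sided, which makes 5% one-sided the likely intent. The 10% outside the bracket may be the two-sided equivalent, or the missing margin mislabelled as a significance level. This largely stands. A reader might infer that the planned false-claim rate is really 10%, twice what it should be. That depends on the less likely reading and is not supported. What remains is that the printed text carries two values and does not say what the 10% is.

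A reader might also infer that 158 proves one-sided 5%, or that the margin was 10 points. Neither follows: one-sided 10% with a margin of about 8.5 points gives 158 as well, and the protocol names no margin. A separate statistical analysis plan may give it. The point here is only that the calculation as printed cannot be confirmed without it.

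Finally, the effect is small. That is correct, and it is why a change of wording is enough.

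**Conclusion.** The dropout step in section 3.2 is wrong as written, and this rests on the protocol's own figures alone: 380 leaves 304 at 20% loss against a stated need of 316, and covers at most 16.8%. The practical effect is modest. It falls mainly on the PPS and on patients lost before any post-dose evaluation. Where it does apply, power is about 78.7% instead of 80.1%, given 85% in both arms, one-sided 5% and an assumed 10-point margin.

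The significance level is stated inconsistently within one sentence. One-sided 5% is the probable intent, but the meaning of the 10% and the margin behind 158 need to be stated. Both faults deserve correction because the text is cheap to put right; neither calls the design into question.

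**What to change.** Keep 380 and correct section 3.2:

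1. Restate the allowance: 380 randomised gives 158 evaluable per group at up to 16.8% dropout, and 152 per group at 20%. Give the power at 152 for the margin actually used (about 78.7% if that was 10 points at one-sided 5%). Note that the loss applies mainly to the PPS, since the FAS keeps later dropouts by LOCF.
2. State a single alpha with its sidedness. The bracket indicates one-sided 5%, which corresponds to a two-sided 90% confidence interval.
3. Say what the 10% denotes, and give the non-inferiority margin used in the calculation. The sponsor should take it from the original calculation and not adopt 10 points merely because that reproduces 158.

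The cost is a reworded paragraph and a slightly less favourable power figure at 20% dropout, with no extra patients. If full cover for 20% is wanted instead, the total becomes 396 (395 if the total is inflated), which is 15 to 16 more patients.

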3.3 Randomized design

Randomization will be carried out using block randomized sequences generated by computer. In this study, sealed envelope system will be used for randomization. In this participating investigators are given randomly generated treatment allocations within sealed opaque envelopes. Once a participant has consented to enter a trial an envelope is opened and the participant is then assigned an ID code and offered the allocated treatment regimen.

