3.4 Blinding level

In this open label study, participants, investigators and outcome assessors will not remain blinded to the treatment.

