5.1 Primary outcome measurements

Clinical cure (short and long term): clinical symptoms (pain and burning sensation rating), signs (pseudomenbran and erythema grade)

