5.2 Secondary outcome measurements

• Clinical improvement rate: (score of symptom and clinical sign at baseline- score of symptom and clinical sign post treatment)/ score of symptom and clinical sign at baseline

• Mycological: Eradication of organism (negative culture and negative microscopy)*

• Safety: Number of patient withdrawals due to adverse reactions; Incidence of adverse reactions (reported as side-effects).

*Candida albicans is found routinely in asymptomatic population, therefore, it would have been inappropriate to use mycological eradication as the primary outcome measure for the study.

The cure is defined as complete clinical response and eradication of Candida spp. at Day 7 or Day 14. A complete clinical response was defined as the complete disappearance of oral candidiasis lesions, and a partial clinical response was defined as ≥60% of clinical improvement rate compared with the score at baseline. <60% of clinical improvement rate and candida persistence, re-infection or species shifts were considered failures. Finally, biologic, local, and general safety was compared between treatments.

Participants will also be required to complete their daily diaries from the start of the treatment period until the end of the treatment period. Blood tests for full blood count and liver and kidney function tests will be conducted at initial assessment and during the final clinic visit (week 4).

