8.3 Research process

Potential participants will undergo preliminary screening for eligibility during visit 1 by investigators, which will include a registered oral medicine specialist. Eligible participants will then undergo initial assessments for review of system (ROS), baseline data collection, which include the symptom scoring, grade of clinical sign of oral candidiasis, measurement of vital signs (temperature, blood pressure and heart rate. ECG), full blood count, kidney function test and liver function test. The candida-related laboratory testing (smear test and fungi culture) will be performed to gather the baseline data of candida infection and colony forming unit count. A daily diary will then be given to record the change of symptoms and occurrence of adverse events and use of topical treatments during the 2-week treatment period. After signing the consent form, participants will be randomly assigned to either the treatment (miconazole mucoadhesive tablet) group or the control (itroconazole capsule) group and the treatment period will start. During this clinic visits, participants will be given 1 weeks’ worth of miconazole mucoadhesive tablet or itroconazole capsules and daily diaries for the fortnight.

In visit 2 of 1week after, the participants will be re-evaluated on the symptom scoring, grade of clinical sign, vital signs, smear test and fungi culture). The participants will repeat 1-week treatment and record the daily diary during the following week. In visit 3 (the following day after the 2-week treatment period) and visit 4 (2-week follow up after treatment ceasing), the participant will be evaluated by performing clinical and laboratory examination as baseline.

Throughout the treatment period, other medication or therapies, such as anti-hypertension drugs, is allowed to be used on an ‘as needed’ basis. During this treatment period, participants will also be required to record their medication intake, including trial interventions, other medications intake and occurrence of adverse events to assist with compliance monitoring and acceptability of intervention. Participants will be asked to return their medication pack to enable the counting of left-overs as well as part of participant adherence monitoring.

[figure not shown]

Figure 2. Outline of trial protocol

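### Section 3.3 opens the allocation envelope before the participant has an ID, and section 3.4 leaves smear and culture reading unmasked: two avoidable weaknesses in an open-label, block-randomised trial

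*Protocol*

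**What the plan says.** On allocation, Protocol section 3.3 states: "Randomization will be carried out using block randomized sequences generated by computer". Under the envelope system, "participating investigators are given randomly generated treatment allocations within sealed opaque envelopes". The order of steps is then fixed: "Once a participant has consented to enter a trial an envelope is opened and the participant is then assigned an ID code", after which the allocated treatment is offered. Section 8.3 agrees that consent comes first: "After signing the consent form, participants will be randomly assigned to either the treatment" or the control group.

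On blinding, section 3.4 says that "participants, investigators and outcome assessors will not remain blinded to the treatment". The only masking in the protocol is in section 11.2, where the data are "analyzed by an independent statistician, who will be blinded to participant allocation".

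On outcomes, section 5.1 gives the primary measure as "Clinical cure (short and long term): clinical symptoms (pain and burning sensation rating), signs (pseudomenbran and erythema grade". In section 5.2, "A complete clinical response was defined as the complete disappearance of oral candidiasis lesions", and cure requires both that response and eradication of Candida at Day 7 or Day 14. Section 5.2 also lists eradication, by culture and microscopy, as a secondary outcome. The introduction to section 5 names Candida elimination among the primary measures.

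**The concern.** Two stated rules are weaker than they need to be.

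**Order of opening.** The people who recruit also hold the envelopes. If they see the arm before the envelope is tied to a participant, an opened envelope can be set aside or used for a different consented patient. Sealing and opacity protect the allocation only until the envelope is opened. With visible treatments and block randomisation, earlier allocations may also hint at later ones. If patients with a better outlook were steered towards one arm, the comparison would be biased at entry, and analysis could not reliably repair it.

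**Masking of laboratory reading.** Symptoms are rated by patients who know their treatment, and lesions are graded by clinicians who know it. Smear and culture are the parts of the outcome easiest to read without that knowledge, yet section 3.4 unblinds every outcome assessor. The trial tests non-inferiority (section 11.2), where a modest shift in measured cure rates can change the conclusion in either direction.

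**Working it through.** **1. What is on record at each step**

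| Step | Record stated in the protocol | Ties envelope to person before the arm is seen? |
|---|---|---|
| Consent | Signed form kept (12.2) | No: shows who consented, not which envelope was theirs |
| Envelope opened | None stated (3.3) | No |
| ID assigned | ID code (3.3) | No: comes after opening |
| Drug dispensed | Dispensing record (7.4); case report forms checked against source (10) | No: comes after opening |

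Section 7.4 has drug handed out in order, but that governs dispensing, not the opening of envelopes.

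**2. Predictability of blocks (illustration)**

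Assumptions that the protocol does not state: 1:1 blocks of one fixed size 2b, known to the investigator; complete blocks within a centre; all earlier allocations there tracked. The last k allocations of a block are all the same arm with probability 2·C(2b−k, b)/C(2b, b). Summing over k = 1 to b gives the expected number known with certainty, 2b/(b+1), which is a share of 1/(b+1).

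- Block of 4 (b = 2): 4/3 = 1.33 per block; 1.33/4 = 33%.
- Block of 6 (b = 3): 6/4 = 1.5 per block; 1.5/6 = 25%.
- Block of 8 (b = 4): 8/5 = 1.6 per block; 1.6/8 = 20%.

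Guessing the arm with more places left in the block would be right 70.8%, 68.3% and 66.6% of the time. Simple randomisation gives 0% certain and 50% guessed.

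**3. Sensitivity of the non-inferiority test to a shift in measured cure (illustration)**

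Inputs from section 3.2: 85% efficacy, one-sided α of 5%, 80% power, 158 per group. The protocol states no margin. A 10-point margin is assumed because it reproduces the stated number:

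n = (1.645 + 0.842)² × 2 × 0.85 × 0.15 / 0.10² = 157.7, rounded up to 158.

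Let the true miconazole rate lie at the margin (75% against 85%) and let unmasked reading add s in its favour, so p = 0.75 + s. Type I error is Φ(s/SE − 1.645), with SE = √[(0.85×0.15 + p(1−p))/158]. For s = 0.01, SE = √[(0.1275 + 0.1824)/158] = 0.0443 and Φ(0.226 − 1.645) = 7.8%.

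For shifts against miconazole, the true rates are equal and p = 0.85 − s. Power is then Φ((0.10 − s)/SE − 1.645).

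| Assumed shift s | Type I error if in favour of miconazole | Power if against miconazole |
|---|---|---|
| 0 | 5.0% | 80.1% |
| 1 point | 7.8% | 71.4% |
| 2 points | 11.7% | 61.6% |
| 3 points | 17.0% | 51.3% |
| 5 points | 31.8% | 31.8% |

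The shifts are invented to show sensitivity. They do not estimate what masking the laboratory would recover, since that covers only the eradication part of cure.

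**The case against.** Open label is a declared choice (title, sections 3.1 and 3.4), and the design has real safeguards: opaque sealed envelopes, consent before opening, retained consent forms, and monitoring against source documents. Serial numbering, lists by centre and mixed block sizes are unstated rather than contradicted. They may sit in randomisation documents not shown, and a block size may properly be kept out of a protocol. All of this stands, so the point rests only on the stated opening order and the stated unblinding of assessors.

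Five stronger readings are tempting and are not supported:

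- *A participant could be swapped or dropped with nothing to show for it.* The signed consent form remains (section 12.2). What is missing is the link from envelope to person.
- *The order of steps pushes such people out of the full analysis set.* Section 11.1 requires randomisation and an evaluation after medication. A person never treated is outside that set whichever step comes first.
- *A definite number of the 380 allocations is predictable.* That needs a known fixed block size and blocking by centre, and the protocol states neither.
- *Laboratory staff are told the arm.* Section 3.4 does not say so, and the ID codes in section 5.3 are compatible with coded specimens. The gap is that the blanket statement makes no exception.
- *Masking the laboratory would make the cure comparison unbiased.* Section 5.1 rests on symptoms and signs, which stay unmasked. At the one-week visit a tablet or its residue on the gum could also show the arm to whoever grades the lesions.

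**Conclusion.** The point holds in a limited form. Section 3.3 fixes an order in which the arm is seen before the envelope is tied to a participant, and no other section supplies that link in advance. The blinded statistician neither enrols nor grades, so section 11.2 does not help. Allocation concealment is weakened, not absent. Section 3.4 leaves smear and culture reading unmasked although it feeds the cure definition in section 5.2 and could be protected easily.

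Neither the size nor the direction of any bias can be derived from the protocol. The 33%, 25% and 20% figures hold only for fixed blocks of 4, 6 and 8 tracked within a centre. The type I error and power figures rest on an assumed 10-point margin and assumed shifts. Both sets show why the safeguards matter and do not measure harm. The change is worth making because it costs little; the present wording does not by itself invalidate the trial.

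**What to change.** **Section 3.3.** Reverse the order: after consent, assign the ID; write ID, date and initials on the next numbered envelope; only then open it. State that everyone whose envelope is opened counts as randomised and is reported as such. This makes the participant flow complete; it does not alter who meets the full analysis set definition in section 11.1.

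**Section 3.4.** Add that smear and culture specimens carry the ID code only and are read without knowledge of the arm.

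**Cost.** Revised wording, numbered envelopes, a brief logging step at each enrolment, and specimen labelling at the nine centres. The protocol does not say who reads the smear; where the treating investigator does, another reader would be needed.

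**What remains.** Self-rated symptoms and lesion grading stay unmasked. Recording the ID before opening also does not stop an investigator guessing the next allocation from earlier ones, so bias is reduced, not removed.
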